## Measures

Screening measures

Families will be asked to complete initial screening questions to determine their eligibility for the research and to describe the study sample. This will include demographic information about the CYP and their parent(s)/carer(s), confirmation of UK residency, information about prescribed psychotropic medication of the CYP and current/previous psychological support received by the CYP. They will also be asked to complete a brief questionnaire to determine if the CYP is experiencing possible symptoms of eating disorders (i.e., the Child Eating Disorder Examination Questionnaire – 8-items; ChEDE-Q8), as well as some questions regarding the extent to which these eating disorder symptoms impair functioning (adapted from the Strengths and Difficulties Questionnaire (SDQ) impact supplement) and a question around current risk (see [Appendix 1](#Appendix1)).

*Child Eating Disorder Examination Questionnaire – 8-items (ChEDE-Q8; Kliem et al., 2017)*

The ChEDE-Q8 is an 8-item self-report measure that evaluates four areas of eating disorder psychopathology: restraint, eating concern, shape concern and weight concern. The ChEDE-Q8 scores range from 0 (absence of the feature) to 6 (feature present every day to an extreme degree). Global mean scores will be calculated, with higher scores indicating higher levels of eating disorder psychopathology. The ChEDE-Q8 has been validated for children aged ≥ 7 years and has been shown to have strict measurement invariance, internal consistence as well as convergent and factorial validity (Kliem et al., 2017).

Baseline only measures

Psychiatric diagnoses

*The Development and Wellbeing Assessment (DAWBA;* Goodman et al., 2000)

This standardised diagnostic instrument is designed to generate ICD-10 and DSM 5 psychiatric diagnoses. The DAWBA provides a probability of the likelihood of a range of mental health disorders. The DAWBA incorporates the Strengths and Difficulties Questionnaire (SDQ), a brief (25-item) emotional and behavioural questionnaire and its impact supplement (Goodman, 1997). The DAWBA (Brøndbo et al., 2012) has been shown to have excellent reliability and validity.

Baseline and post-intervention measures

### Eating disorder psychopathology

*Eating Disorder Examination Questionnaire (EDE-Q; Fairburn & Beglin, 2008)*

CYP will be asked to complete the self-report version of the EDE-Q. The EDE-Q is a questionnaire which assesses core eating disorder-specific attitudes and behaviours (Bryant-Waugh et al., 1996). The EDE-Q derived from the widely used Eating Disorder Examination (Fairburn & Cooper, 1993), considered the gold standard for assessing eating disorder cognitions and behaviours. The EDE-Q consists of 28 items which assess the level of eating disorder psychopathology during the last 28 days, across four subscales: restrain (5 items), eating concern (5 items), weight concern (5 items) and shape concern (8 items). A global score is calculated from the average of the four subscales. Subscale items of the EDE-Q are rated on a 7-point scale, ranging from 0 (no restraint/concern) to 6 (restraint present everyday/extreme concern), thus higher scores indicate greater severity or frequency of eating disorder symptoms. The EDE-Q has good psychometric properties including good internal consistency, adequate test-retest reliability, good internal consistency, as well as high convergent and discriminant validity (Berg et al., 2012).

*Parent Eating Disorder Examination Questionnaire (PEDE-Q; Loeb, 2008)*

Parents will be asked to complete the parent-report version of the EDE-Q, known as the PEDE-Q. The PEDE-Q is a 29-item measure that assesses parental perceptions of the severity of their child's eating disorder symptoms. The PEDE-Q values the perspective of a parent or guardian, as often they have observed certain behaviors that a child will not report. There are four subscales within the PEDE-Q, including: Restraint, Eating Concern, Shape Concern, and Weight Concern. The PEDE-Q has good psychometric properties and provides incremental information that can aid in the assessment of adolescents with eating disorders (Drury et al., 2023).

*The Clinical Impairment Assessment (CIA; Bohn et al., 2008)*

The CIA is a 16-item, self-report questionnaire designed to measure psychosocial impairment due to eating disorder features in the past 28 days. Items are rated on a 4-point Likert-like scale, ranging from 0 (not at all) to 3 (a lot). The 16 items cover impairment in domains of life that are typically affected by eating disorder psychopathology: mood and self-perception, cognitive functioning, interpersonal functioning and work performance. A CIA global score is calculated as a severity index (ranging from 0 to 48), which higher scores indicating greater severity of clinical impairment. The CIA has demonstrated high levels of internal consistency, test-retest reliability, sensitivity to change, construct validity, and discriminant validity (Bohn et al., 2008; Reas et al., 2010). The CIA has been slightly modified to make it applicable to CYP (e.g., item 4 asks about school performance as opposed to work performance).

%Weight-for-height

CYP, and their parents/carers, will be asked to report on the CYP’s body weight and height so that their %weight-for-height (Weight x 100 reference weight for CYP of the same height) can be calculated.

Depression and anxiety symptomatology

*The Revised Child Anxiety and Depression Scale (RCADS; Chorpita et al., 2000)*

The self-report and parent-report versions of the RCADS will be used to measure the CYP’s anxiety and depression symptoms. It is a 47-item questionnaire for 8-18 year olds, which is sub-divided into six scales: separation anxiety disorder, social phobia, generalised anxiety disorder, panic disorder, obsessive compulsive disorder and low mood (major depression). Each item is scored on a 4-point Likert scale from 0 (never) to 3 (always). In addition to the subscales, the RCADS can be used to calculate a total anxiety score and total anxiety and depression score. The RCADS has good reliability on subscales and total scale, with internal consistency of adequate to excellent across the different subscales (Chorpita et al., 2005). The measure also has good test-retest reliability, and good convergent and concurrent validity (Chorpita et al., 2005; Donnelly et al., 2019).

If it is decided to no longer use the DAWBA following the pilot, families will be asked to complete the Strengths and Difficulties Questionnaire (SDQ) instead.

*The Strengths and Difficulties Questionnaire (SDQ; Goodman, 1997)*

The self-report and parent-report versions of the SDQ will be used to assess the CYP’s psychological wellbeing. The SDQ is brief (25-item) emotional and behavioural questionnaire for CYP aged 2-17 years of age. The 25 items comprise 5 scales of 5 items each, each rated on a 3-point Likert scale ranging from 0 (‘not at all’) to 2 (‘certainly true’). The scales include: emotional symptoms, conduct problems, hyperactivity/inattention, peer relationship problems, prosocial behaviour. The first four subscales can be summed to provide a total difficulties score. The SDQ also has an ‘impact supplement’ which assesses the functional impairment of the identified problems across four domains (school, home, friendships, leisure). Impact items are scored on a four-point scale from 0 (‘not at all’) to 2 (‘a great deal’). The reliability and validity of the SDQ has been established (Goodman, 2001; Muris et al., 2003).

Session-by-session measures throughout intervention

*Eating Disorder-15 for Youth (ED-15-Y; Accurso & Waller, 2021a; Accurso & Waller, 2021b)*

The ED-15-Y is a brief measure of eating disorder psychopathology over the past week for children and adolescents aged ≥8 years. The measure was adapted from the adult ED-15 (Tatham et al., 2015). The ED-15-Y includes 10 attitudinal items (measured on a 1-5 scale) and five behavioural items (frequency of dieting, binge eating, vomiting, laxative use, driven exercise), which are also rated on a five-point scale. The ED-15-Y has demonstrated excellent reliability, validity and sensitivity to change over time in CYP with eating disorders (Accurso & Waller, 2021).

*Goal Based Outcomes (GBOs; Law, 2006)*

The GBO scale is an idiographic outcome measure that is used to track progress during intervention. In their first guidance session, CYP, and/or their parents/carers, will be asked to identify up to 3 intervention goals relating to the CYP’s eating disorder difficulties. They will be asked to rate on a scale from 0-10 where they are in terms of achieving this goal; with 0 reflecting no progress towards the goal and 10 meaning that the goal has been fully reached. Families will then rate each goal as part of the routine outcome measures for each session. Goal-based outcomes have been shown to improve treatment retention, clinical outcomes and client progress (Delgadillo et al., 2018; Tryon et al., 2018).

*Outcome Rating Scale (ORS)/Child Outcome Rating Scale (CORS; Duncan et al., 2006)*

The ORS/CORS is a four-item scale that assesses areas of life functioning that change in response to therapeutic intervention: symptom distress, interpersonal wellbeing, social life, and overall wellbeing. Each dimension is displayed as a visual analogue scale ranging from 0 to 10 (10 = better functioning). The ORS is designed for children aged 13-18 years and the CORS can be completed by children aged 6-12 years; the CORS has the same format but contains more child friendly language and smiley and frowning faces. The ORS/CORS has good concurrent validity with other outcome measures, and high internal consistency and test-retest reliability (Duncan et al., 2006).

*Strengths and Difficulties Questionnaire Session by Session (SDS SxS; Hall et al., 2015)*

The SDQ SxS measure is a modified form of the SDQ Impact Supplement that is intended for intervention progress monitoring. Self-rated items assess young people’s improvement, impact of problems on everyday life in the present and anticipated improvement in the future.

CYP will be asked to provide their weight every week for risk and medical monitoring.

Post-treatment only measures

*The Strengths and Difficulties Questionnaire (SDQ; Goodman, 1997)*

The self-report and parent-report versions of the SDQ will be used to assess the CYP’s psychological wellbeing. The SDQ is brief (25-item) emotional and behavioural questionnaire for CYP aged 2-17 years of age. The 25 items comprise 5 scales of 5 items each, each rated on a 3-point Likert scale ranging from 0 (‘not at all’) to 2 (‘certainly true’). The scales include: emotional symptoms, conduct problems, hyperactivity/inattention, peer relationship problems, prosocial behaviour. The first four subscales can be summed to provide a total difficulties score. The SDQ also has an ‘impact supplement’ which assesses the functional impairment of the identified problems across four domains (school, home, friendships, leisure). Impact items are scored on a four-point scale from 0 (‘not at all’) to 2 (‘a great deal’). The reliability and validity of the SDQ has been established (Goodman, 2001; Muris et al., 2003).

*Acceptability questionnaire*

Families’ satisfaction with the intervention will be assessed using a seven-item questionnaire adapted from Creswell and colleagues (2010). CYP, and their parents/carers, will be asked to rate five areas of satisfaction on five-point Likert scales: change in the CYP’s disordered eating, satisfaction with the programme, the help received, overall satisfaction and whether they would recommend the approach to others. Families will also be asked about satisfaction with the amount of help received and the methods through which this was delivered. Families will also have the opportunity to provide qualitative feedback in response to open-ended questions assessing which elements of treatment participants found most and least helpful, and their suggestions for improvement (see [Appendix 3](#Appendix3)).

### Optional qualitative interview

All CYP, and their parents/carers, who start the treatment will be invited to attend separate optional qualitative interviews to explore their experience of receiving the intervention and acceptability of the treatment approach. Families who dropout of the study, and explicitly state that they do not wish to be contacted, will not be invited to take part.

Interviews will cover what families found helpful/unhelpful about the intervention, views on the mode, content and structure of the treatment and suggestions for improvement. An indicative topic guide can be found in [Appendix 4](#Appendix4). Qualitative interviews will be conducted over videocall or via the telephone by a member of the research team who did not deliver the treatment (e.g., an Honorary Research Assistant).

*Treatment completion/drop-out rates*

Information regarding rates of recruitment, retention, completion of measures and proportion of sessions attended by the participants will be recorded to examine feasibility.

## Data analysis

### Quantitative analysis

Statistical analyses will be performed using IBM SPSS Statistics 27. Descriptive analyses will be used to characterise the sample, to examine the participant flow through the study and attrition rates at each stage, and to assess satisfaction with the intervention.

Baseline and post-intervention measures

Symptom change will be measured by comparing scores at baseline and end of treatment. In order to ensure that the outcomes are not affected by attrition, the analyses will be conducted using Intention to Treat methods. Paired t-tests will be used to compare differences from the baseline measures to end of treatment, and Cohen’s *d* will be used to determine effect sizes (small effect ≥ 0.2, medium effect ≥ 0.5 and large effect ≥ 0.8).

Outcomes will also be evaluated on an individual level using Jacobson and Truax (1991)’s indices of meaningful change: Reliable Change Index (RCI) and Clinically Significant Change (CSC). Achievement of RCI indicates that the observed change is unlikely to be due to measurement error, and achievement of CSC indicates that change is substantial, relative to the clinical and non-clinical ranges of scores.

Session-by-session measures

Weekly measures (ED-15-Y, GBOs, ORS/CORS and SDQ SxS) will be analysed visually.

Acceptability

The feasibility and acceptability of the guided self-help intervention will be evaluated by analysing the treatment satisfaction of participants using both questionnaire measures and qualitative interviews.

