| Baseline and outcome measures | Baseline and post-intervention measures:   - Eating Disorder Examination Questionnaire self-report (EDE-Q) and parent-report (PEDE-Q) - Clinical Impairment Assessment (CIA) - %Weight-for-height - Revised Child Anxiety and Depression Scale (RCADS) - DAWBA (baseline only) or SDQ (total and impact supplement)   Session-by-session measures:   - Eating Disorder-15 for Youth (ED-15-Y) - Goal Based Outcomes (GBOs) - Outcome Rating Scale (ORS)/Child Outcome Rating Scale (CORS) - SDQ Session-by-session (SDQ SxS)   Post-intervention measures only:   - Acceptability questionnaire - Optional qualitative interview |
| Treatment period | 3 months maximum |
| End of study | The final post-intervention assessment (12 weeks after baseline measures) for the final participant or the last qualitative interview with the final participant, whichever occurs last |

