Guided self-help interventions are the first step treatment for adults with bulimia nervosa and binge eating disorder (National Institute for Health and Care Excellence, 2017), and have proven efficacy for CYP with anxiety and depression (Bennett et al., 2019; Thirlwall et al., 2013), which often co-occur with eating disorders (Keski-Rahkonen & Mustelin, 2016). However, child and adolescent eating disorder services do not routinely use guided self-help interventions as they have not been sufficiently researched. The limited research that does exist suggests that guided self-help interventions have the potential to be effective for this patient group. In their randomised controlled trial (RCT), Schmidt et al. (2007) compared cognitive behavioural therapy (CBT) guided self-care with family therapy in 85 adolescents with bulimia nervosa and related disorders, and the outcomes indicated no difference between groups, with the guided self-care showing greater impact at 6 months and being more cost-effective. Lock et al. (2021) conducted a pilot RCT of 40 adolescents with anorexia nervosa which compared online family-based guided self-help to family-based treatment delivered via videoconferencing. The results suggested that family-based guided self-help was acceptable to families and led to improvements in terms of both weight gain and global eating disorder psychopathology. However, both of these interventions remain in the domain of research and are not readily available for CYP with eating disorders in the UK.

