## Participants

This study will look to recruit CYP (aged 8-19 years) with impairing symptoms of eating disorders, and their parents/carers. In line with previous case series research (da Luz et al., 2017; Dumont et al., 2019), the aim will be to recruit approximately 10 eligible families to receive the CBT guided self-help intervention.

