**Eligibility criteria**

### Children and young people

Inclusion criteria

The inclusion criteria for CYP:

1. Aged 8-19 years
2. Has a threshold or sub-threshold eating disorder (anorexia nervosa, bulimia nervosa, binge eating disorder and otherwise specified feeding and eating disorder [OSFED]) which impairs their psychosocial functioning
3. Is a UK resident
4. Have a parent/carer who is also willing to take part in the study

Exclusion criteria

The exclusion criteria for CYP:

1. Does not speak/understand English sufficiently well to access the measures and intervention materials. This is primarily due to limited funding capacities for interpreters
2. Has an intellectual disability at a level meaning that they cannot access the measures and/or intervention. This will not be defined by IQ, but by clinical judgement. CYP will not be excluded because of the presence of intellectual disability per se, but because of being unable to access the materials. Ability to participate may be different for younger children who are less able, whose parents complete the materials, compared to older children who need to complete the materials themselves. If the intellectual disability is identified during the initial assessment (through clinical judgement), young people will be referred to other more appropriate services as necessary (with agreement of the family)
3. Questionnaire indicates acute risk not considered suitable for the trial due to the clinical need for immediate and/or specialist intervention, e.g., rapid weight loss, very low mood, high medical or psychiatric risk, acute suicidality, recurrent or potentially life limiting self-harm and/or significant safeguarding concerns (i.e., if the child has a child protection plan and/or is on the child protection register, and/or the research team consider the child to be suffering, or likely to suffer, significant harm)
4. If they have been prescribed psychotropic medication, the dosage must have been stable for the past two months
5. Currently receiving other overlapping psychological support/interventions
6. Does not have access to a telephone or laptop/computer which can be used for the interviews and guidance sessions

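### The pooled pre-post change in %weight-for-height has no common direction of benefit across the enrolled diagnoses, so its sign and effect-size label can reflect case mix

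*Protocol*

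**What the plan says.** The Study summary places %"Weight-for-height" among the baseline and post-intervention measures, alongside the EDE-Q, PEDE-Q, CIA and RCADS. The Measures section explains that families "will be asked to report on the CYP’s body weight and height so that their %weight-for-height" can be calculated. It is a percentage of the reference weight for a young person of the same height. No target value or direction of improvement is attached to it.

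Under Data analysis, Quantitative analysis, the part on baseline and post-intervention measures treats the comparison of the two time points as the measure of symptom change. It then states: "Paired t-tests will be used to compare differences from the baseline measures to end of treatment". Cohen's d is labelled at 0.2, 0.5 and 0.8. RCI and CSC follow as an individual-level evaluation. Nothing is split by diagnosis or starting weight.

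The inclusion criterion reads "Has a threshold or sub-threshold eating disorder (anorexia nervosa, bulimia nervosa, binge eating disorder", and continues to OSFED. There is no weight criterion and no quota by diagnosis. On sample size, "the aim will be to recruit approximately 10 eligible families".

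The only statement about the direction of weight change is in the Rationale. There a cited pilot trial in adolescents with anorexia nervosa is said to have "led to improvements in terms of both weight gain and global eating disorder psychopathology".

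**The concern.** A pre-post mean can be read as symptom change only if a shift in one direction means the same thing for each person averaged. The EDE-Q and CIA meet that condition, because the protocol says that higher scores are worse. %Weight-for-height does not, because participants may start on either side of the reference weight and the protocol does not say what counts as improvement for whom.

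Two misreadings follow. A gain among participants for whom gain is the aim can be offset by change in the others and be reported as little or no effect. Conversely, a rise that comes only from participants for whom gain is not an aim can be labelled as an effect of the intervention. Preliminary effectiveness is part of the primary objective, and this is the only physical measure among the baseline and post-intervention outcomes.

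**Working it through.** The protocol gives no SD, expected change or power for %weight-for-height, so there is no planned figure to reproduce. The numbers below illustrate the mechanism and do not predict results.

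**From the protocol:** about 10 participants in one group; mixed diagnoses; a paired t-test on the whole sample; d labels at 0.2, 0.5 and 0.8.

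**Assumed:** the case mix, the mean changes, the within-group SD of change, and d computed as mean change divided by the SD of change. The protocol does not say which SD it will use.

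**Formulas.** Let a fraction p of participants change by a on average and the rest by b, with within-group SD s.
- Pooled mean = p·a + (1-p)·b
- Pooled SD of change = √[s² + p(1-p)(a-b)²]
- d = mean / SD

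**Step 1: 5:5 mix, s = 5.**
- a = +6, b = -4: mean = 0.5×6 - 0.5×4 = +1.0; SD = √(25 + 0.25×100) = 7.07; d = 0.14, below the label for a small effect. Simulated samples of 10 give a median d of 0.14, with p<0.05 in about 1.5% of runs.
- a = 0, b = +4: mean = +2.0; SD = √(25 + 0.25×16) = 5.39; d = 0.37. The simulated median is 0.38, with p<0.05 in about 16 to 17% of runs. This earns the label small effect although the first group did not change.

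**Step 2: vary the mix, s = 3, with participants with anorexia changing by +5.** d and the chance of p<0.05 are from 40,000 simulated samples of 10.

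| Change in others | With anorexia | Pooled mean | Median d | Chance of p<0.05 |
| --- | --- | --- | --- | --- |
| -5 | 2 of 10 | -3.0 | -0.59 | 29% (as a fall) |
| -5 | 5 of 10 | 0.0 | 0.00 | about 0% |
| -5 | 8 of 10 | +3.0 | +0.59 | 29% (as a rise) |
| 0 | 2 of 10 | +1.0 | 0.28 | 8% |
| 0 | 5 of 10 | +2.5 | 0.65 | 40% |
| 0 | 8 of 10 | +4.0 | 1.12 | 90% |
| +5 | any of these | +5.0 | about 1.7 | over 99% |

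The formula agrees: for the first row, SD = √(9 + 0.16×100) = 5 and d = -3/5 = -0.60. Within each of the first two blocks the group changes are identical and only the mix differs, yet the label moves from small to large and the sign can reverse. Only when both groups move alike does the mix cease to matter.

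**Step 3: change the denominator.** If d used the baseline SD, and that were 15 points (assumed), the Step 1 values would be 1/15 = 0.07 and 2/15 = 0.13. Both fall below 0.2. The choice of denominator alters the label but not the dependence of the mean on case mix.

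**The case against.** **Scope is inferred.** The t-test sentence does not name %weight-for-height, and the surrounding language of scores and symptoms suits questionnaires. An unseen analysis plan might treat weight separately. That is possible, but the sentence sits under the heading for baseline and post-intervention measures, weight is listed as one of them, and the protocol gives it no other analysis.

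**Direction of benefit is thinly documented.** A reader might infer that the protocol regards a rise in weight as no improvement in bulimia or binge eating disorder. It does not say so. Its one remark on direction describes another trial, in anorexia only. Nor does diagnosis establish weight status, since sub-threshold cases and OSFED are eligible. This objection stands. What survives is narrower: no common direction is stated, and eligibility does not supply one.

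**RCI and CSC.** A reader might infer that these suffer from the same cancellation. They do not, because they are applied person by person. Their separate difficulty is that the protocol gives neither a clinical range nor a reliability for %weight-for-height.

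**Size and importance.** The changes, SDs and mixes are assumed, and d depends on an unstated denominator. The second example in Step 1 reaches p<0.05 in only about one run in six. The measure is one of several in an uncontrolled feasibility series, is not designated primary, and no progression rule or sample size rests on it. This also stands and limits the severity.

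**Conclusion.** The point holds as one of interpretation. Followed as written, the protocol produces one signed mean and one effect label for a measure without a common direction of benefit, in a sample with no control on case mix. That result should not be read as preliminary effectiveness.

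It would go too far to call the pooled change uninterpretable in all circumstances: if the recruits turned out to be homogeneous in starting weight, it could be read. Eligibility simply does not ensure that. It would also go too far to say that the study's conclusions as a whole are at risk, since the EDE-Q, PEDE-Q, CIA and RCADS are unaffected.

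Under the stated assumptions the label can miss a 6-point gain in half the sample (d about 0.14) or show a small effect when that half did not change (d about 0.38). With a larger baseline SD as the denominator, both values shrink. This is a should-fix.

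**What to change.** In Data analysis:
- Take %weight-for-height out of the pooled paired t-test and Cohen's d. Keep the pooled analysis for the scales with one direction (EDE-Q, PEDE-Q, CIA, RCADS).
- List each participant's diagnosis, baseline value and 12-week value.
- Summarise change descriptively, without a test, by recorded diagnosis. The clinical team should set the grouping, and the direction of benefit for each group, before any 12-week data are seen. The grouping needs a place for sub-threshold participants who have no recorded diagnosis.
- Use RCI and CSC for weight only if the clinical range and the reliability are specified.

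A test or confidence interval in a subgroup would add little: with 5 participants and an SD of change of 5 points (assumed), the 95% half-width is 2.776×5/√5 = 6.2 points. Grouping by diagnosis is preferable to grouping by a service's underweight classification, because the screening questionnaires in Appendix 1 ask for diagnosis and no listed item records such a classification.

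The cost is a few sentences and no new data. The drawbacks are that weight will have no single summary effect size and that the groups will be small.

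### Small, medium and large labels are fixed on a Cohen's d point estimate from about 10 pre/post pairs, with no interval and no named standardiser, so they cannot tell no effect from a large one

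*Protocol*

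**What the plan says.** The Quantitative analysis section of the protocol sets out the group-level comparison: "Paired t-tests will be used to compare differences from the baseline measures to end of treatment". In the same sentence, Cohen's d "will be used to determine effect sizes (small effect ≥ 0.2, medium effect ≥ 0.5 and large effect ≥ 0.8". The comparison covers the measures taken at both time points: EDE-Q, PEDE-Q, CIA, %weight-for-height, RCADS and SDQ.

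The Participants section gives the sample size: "the aim will be to recruit approximately 10 eligible families". Its stated basis is precedent ("In line with previous case series research"), and no precision or power calculation is given. The Study summary lists 10 under the maximum sample size and makes preliminary effectiveness part of the primary objective.

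The protocol does not say which SD divides the mean change, whether a small-sample correction is applied, or whether d is reported with an interval. It does plan two individual-level indices beside the group analysis, the Reliable Change Index and Clinically Significant Change.

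**The concern.** The protocol commits the study to turning a point estimate into a verbal grade. With about 10 pairs, the sampling error of d is larger than the gaps between the cut-offs (0.2 to 0.5 to 0.8). The grade can then move by one or two steps through chance alone, and nothing beside it shows this.

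Two further features make the grade hard to read. Cohen's d for paired data can be divided by the SD of the changes or by the SD of the scores, and the two can earn different labels from the same data. Plain d also overestimates its target in small samples.

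At stake is the statement on preliminary effectiveness. A report that the intervention had a medium or large effect on some measures would sound like a finding when the data may be compatible with no change.

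**Working it through.** **Inputs.** n = 10 pairs (Participants; Study summary). Cut-offs 0.2, 0.5 and 0.8 (Quantitative analysis). The protocol states no power, alpha or target precision, so there is no figure of its own to reproduce. Assumptions: normally distributed changes; d = mean change / SD of change in steps 1 to 3, because no divisor is stated; and, in step 4, equal SDs before and after and a range of pre/post correlations r, since the protocol gives none.

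**Step 1, interval for an observed d.** Put t = d√n with 9 degrees of freedom. Find the noncentralities at which the noncentral t distribution function at t equals 0.975 and 0.025, and divide each by √n.

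| Observed d | t = d√10 | 95% CI |
|---|---|---|
| 0.2 | 0.63 | -0.43 to 0.82 |
| 0.5 | 1.58 | -0.17 to 1.15 |
| 0.8 | 2.53 | 0.07 to 1.50 |

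An estimate on the medium boundary is compatible with a small worsening and with an effect well above the large cut-off. An estimate on the large boundary is compatible with one below the small cut-off.

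**Step 2, how often chance earns a label.** With no true change, d√n follows a t distribution with 9 degrees of freedom.
- P(|d| ≥ 0.2) = 0.543, P(|d| ≥ 0.5) = 0.148, P(|d| ≥ 0.8) = 0.032.
- Half of each is in the direction of improvement: 0.271, 0.074 and 0.016.

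With a true d of 0.5 (noncentral t), P(estimate ≥ 0.5) = 0.517 and P(estimate ≥ 0.8) = 0.225. A truly medium effect is graded below medium in about 48% of samples and large in about 22%.

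**Step 3, small-sample bias.** The Hedges factor is J = Γ(df/2) / [√(df/2) · Γ((df-1)/2)]. With df = 9, J = 0.9139, and 1/J = 1.094, an overstatement of 9.4%. Corrected values of 0.2, 0.5 and 0.8 are 0.183, 0.457 and 0.731. A label changes only if d lies in 0.200–0.219, 0.500–0.547 or 0.800–0.875.

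The results are not special to exactly 10 pairs:

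| n | CI for d = 0.5 | CI for d = 0.8 | No true change: P(\|d\| ≥ 0.2), P(\|d\| ≥ 0.5) | Bias |
|---|---|---|---|---|
| 8 | -0.25 to 1.22 | -0.03 to 1.59 | 0.589, 0.200 | 12.6% |
| 10 | -0.17 to 1.15 | 0.07 to 1.50 | 0.543, 0.148 | 9.4% |
| 12 | -0.11 to 1.09 | 0.13 to 1.44 | 0.503, 0.111 | 7.5% |

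**Step 4, the divisor.** With equal SDs, SD of change = SD of scores × √(2(1 - r)). The SD-of-change d is therefore 1/√(2(1 - r)) times the score-SD d.

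| Assumed r | Ratio | A score-SD d of 0.40 becomes |
|---|---|---|
| 0.3 | 0.85 | 0.34 (small) |
| 0.5 | 1.00 | 0.40 (small) |
| 0.7 | 1.29 | 0.52 (medium) |
| 0.8 | 1.58 | 0.63 (medium) |

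The choice of divisor can matter more than the 9% bias, and it works in either direction.

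**Step 5, does a score-SD divisor rescue the labels?** Take r = 0.8 and treat it as known. An SD-of-change d of 0.8 (0.07 to 1.50) is a score-SD d of 0.8/1.581 = 0.51, with limits 0.07/1.581 = 0.04 and 1.50/1.581 = 0.95. Even under this favourable assumption, a medium grade spans near zero to large.

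**The case against.** The strongest reply is that the standardiser, the small-sample correction and the intervals are details commonly left to a statistical analysis plan, and none is at hand. That stands: their absence is not in itself an error. What remains is the rule that the protocol does fix, which grades a point estimate by three cut-offs at this sample size.

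A second reply is that effect is not judged by d alone. The Reliable Change Index, Clinically Significant Change and visual review of the weekly measures are also planned. That is true, but these describe individuals or trajectories and do not make the group-level grade more reliable.

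Two stronger readings are tempting and are not supported.
- A reader might infer that d will be inflated and the effect overstated. This needs an SD-of-change divisor and a correlation above 0.5, and the protocol gives neither; at r = 0.3 the ratio is 0.85. The Withdrawal section also carries the last measure forward. Where that measure is the baseline, the change is zero, which pulls the mean change toward zero and works against the 9% bias.
- A reader might infer that paired t-tests on many scales, with no lead outcome, are a multiplicity error. The protocol ties no alpha, significance threshold or success rule to those tests. The Objective and purpose section calls the study preliminary, so there is no familywise claim to protect.

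Nor does any section say that d will be used to size a later trial. The framework text in the protocol links progression to feasibility and acceptability.

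**Conclusion.** The point holds in this form: at about 10 pairs, the 0.2/0.5/0.8 labels on a bare Cohen's d cannot separate no effect from a large one. The main evidence is the interval of -0.17 to 1.15 around an observed 0.5, and the 54% and 15% chances of reaching the small and medium cut-offs in absolute value when nothing has changed.

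Those figures assume normal changes and an SD-of-change divisor. With a score-SD divisor the chance percentages would be lower if r exceeds 0.5 and higher if r is below 0.5. Step 5 shows that the label stays uninformative at r = 0.8.

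The upward bias of about 9% is real but secondary. The undefined divisor can matter more. The net direction of error cannot be settled from the protocol, so the fault is imprecision and an undefined scale, not a demonstrated overstatement.

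**What to change.** Amend the Quantitative analysis section as follows.
- For each baseline/post measure, report the mean change in scale points with its 95% CI as the main result. At n = 10 the half-width is 2.262/√10 = 0.72 times the SD of change.
- Give the effect size on a named standardiser (baseline or averaged SD), with the small-sample factor (0.914 at n = 10) and a 95% CI.
- Drop the small/medium/large labels, or tie them to the interval by stating which grades it covers.
- Describe the paired t-tests as exploratory.

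Naming one lead clinical outcome or omitting p-values would be a matter of preference, and the point does not depend on either.

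The cost is a change of wording, with no extra data and no burden on families. The reported effect sizes will be slightly smaller from the correction and visibly less certain.
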